# Evaluation of an International Classification of Functioning, Disability and Health-based rehabilitation for thermal burn injuries: a prospective non-randomized design

**DOI:** 10.1186/s13063-019-3910-6

**Published:** 2019-12-19

**Keywords:** Rehabilitation, Thermal injuries, Burn injuries, ICF

## Abstract

**Background:**

Severe burn injuries result in relevant restrictions of physical capacity as well as psychological and social integrity and require a specialized rehabilitation. There is a common agreement, among national as well as international burn associations, that burn rehabilitation is a complex, dynamic process which needs an interdisciplinary and specialized treatment team. There is wide agreement that more research is needed in this field.

**Methods/design:**

The aim of the study is to examine the effectiveness and efficiency of our new ICF (International Classification of Functioning, Disability and Health)-based rehabilitation for thermal injuries. Because of ethical reasons, we have chosen a prospective non-randomized design, which takes place at two different rehabilitation centers. At center A, a newly developed ICF-based rehabilitation program was established; at rehabilitation center B, a well-established rehabilitation program has existed for 20 years and is used as reference. The *primary research question* addresses the “Pre-post comparison of the physical and psychological outcome measurements,” *secondary question I* looks at the “Examination of the non-inferiority of the new treatment concept with the established concept,” and *secondary question II* is the “Analysis of the rehabilitation process based on the rehabilitation cycle.”

Only patients of the two burn rehabilitation centers who are insured by workers’ compensation will be asked to participate in this study to avoid outcome bias by insurance status. A physical examination (physical working capacity testing, grip strength, range of motion, and scar evaluation by Cutometer and Vancouver Scar Scale) and a standardized questionnaire battery (Burn Specific Health Scale-Brief , Short Form 36, Impact of Event Scale-Revised, the German version of the Symptom Checklist, the Freiburg Social Support Questionnaire, Patient/Client Satisfaction Questionnaire, Disabilities of the Arm, Shoulder and Hand, and Lower Extremity Functional Scale ) measure physical and psychological conditions. Data will be taken on admission, during stay, and on discharge of the rehabilitation program and at follow-up 3 and 12 months after discharge. A minimum of 162 participants will be enrolled in this clinical longitudinal, prospective, observational study.

**Discussion:**

The proof of the effectiveness of the ICF-based rehabilitation program for thermal injuries will give evidence in a comprehensive way for the first time in this field. As result, a standardized rehabilitation concept will be introduced, which can be provided to other rehabilitation institutions treating thermal injuries.

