### Participants

The participants are admitted to the two burn rehabilitation centers in Germany dependent on proximity to their place of residence and availability of a contemporary treatment capacity. Preliminary analyses revealed an overall similarity between the both programs except for small differences: The rehabilitation program in center A contains more occupational therapy; at center B the program contains additional balneotherapy, which involves treatment of the skin by bathing in natural mineral water. Center A is located at the campus of a level 1 trauma center, whereas center B is located in a health resort. The duration of the rehabilitation is planned for 3 weeks in both facilities and can be extended individually.

Only patients of the two burn rehabilitation centers who are insured by workers’ compensation (*Deutsche Gesetzliche Unfallversicherung*) are asked to participate in this study to avoid outcome bias by insurance status. This approach is described in other studies for work-related burn injuries [11] or other orthopedic injuries [17]. This effect is described in terms of satisfaction, pain, functional measures, return to work rate, and adverse events [18].

To start a rehabilitation program, the acute treatment must be completed, and no surgical interventions should be planned during the rehabilitation period. Mostly stable skin and scar conditions are essential to initiate a multimodal treatment to support scar maturing. In case of residual defects, healing under conservative treatment should be expected within a short time. An additional requirement is a sufficient cardio-pulmonary exercise capacity. Table 2 presents the inclusion and exclusion criteria for the study.

**Table 2 Tab2:** Inclusion and exclusion criteria for the present study

Inclusion criteria	Written consent
	Sufficient knowledge of German in speech and writing
	Age ≥ 18 years Work-related accident
Exclusion criteria	Serious cognitive impairment (e.g., advanced dementia, acute psychosis, traumatic brain injury)
	Declining of the study

Data will be collected on prepared case report forms (CRFs) and by questionnaires and will be entered continuously into an Access database.

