#### Primary research question

Do the patients benefit from the rehabilitation program regarding their physical and psychological health conditions? Furthermore, are the changes steady after rehabilitation?

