##### Hypotheses

The alternative hypothesis (H1) is as follows:
Physical and psychological outcome measures are enhanced after burn rehabilitation compared to measures before rehabilitation.Physical and psychological outcome measures are enhanced 3 and 12 months after rehabilitation compared to measures before rehabilitation.

The null hypothesis (H0) is as follows:
Physical and psychological measurements are not improved after the burn rehabilitation compared to measures before rehabilitation.Physical and psychological outcome measures are not enhanced 3 and 12 months after rehabilitation compared to measures before rehabilitation.

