## Outcomes

### Initial patient characteristics

The patient demographics measured include age, gender, race/ethnicity, family status, and employment status. Medical characteristics include diagnosis and therapies, total body surface area (TBSA), partial thickness and full thickness burns, Abbreviated Burn Severity Index (ABSI), inhalation trauma, pneumonia or sepsis, other diagnoses, and therapies.

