##### Statistical methods

Data will be collected continuously. For the statistical analysis, data will be checked for a normal distribution. Data are expressed by means with standard deviations and medians with interquartile range as appropriate. Categorical variables will be expressed as percentages.

Pre-post comparison (T1–T2) of the outcome measures will be tested by paired one-sided *t* tests. Longitudinal treatment effects will be tested by paired one-sided *t* tests between T1 and T3 and between T1 and T4.

The non-inferiority between the two centers will be proved with a power of 0.80 if differences are smaller than 0.4 standard deviation. Since randomized assignment to the centers is not possible, a potential selection bias between the samples will be matched by age, gender, TBSA, ABSI, and inhalation trauma. In case of an imbalance of the two samples, the analysis will be made along the procedure of propensity score matching.

A descriptive analysis of the patients’ rehabilitation goals and their linkage to the ICF categories will be performed. Patients’ and therapists’ assessments of goal achievement will be compared. The mean frequency of changing goals during the course of rehabilitation will be obtained. Furthermore, patients’ satisfaction with rehabilitation will be assessed with a qualitative interview, which will be evaluated by content, and the results of the CSQ-8 will be expressed by means and standard deviations.

The statistical evaluation will be carried out in cooperation with the statistician who participated in the design of the study (see Acknowledgements).

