## Discussion

The primary focus of this study is to evaluate the rehabilitation program of two different burn rehabilitation centers. Since there is consensus in the burn literature that outcome is multidimensional for burn survivors, we included a broad spectrum of outcome parameters for the pre-post comparison. We chose the outcome measures along the ICF concepts of body function and structure (exercise capacity, muscle function, scar assessment), personal and environmental factors (mental health, social support), and activities and participation (simple activities, activities of daily living, return to work) in order to get a holistic view about the impact of burn injuries and the treatment necessities.

The instruments we chose are predominantly burn-specific (e.g., the BSHS-B) or frequently used in other burn injury studies (e.g., the SF-36 and IES-R) to enable better comparison with other studies. Instruments used for the evaluation of body function and structure are standard assessments such as the PWC, muscle function, and grip strength or commonly used instruments for scar assessment like the VSS und the Cutometer® MPA 580. The assessment will be conducted before and after the rehabilitation program and at two follow-up points (3 and 12 months after rehabilitation). The long follow-up period was chosen to prove the long-term effect of the rehabilitation program on the wellbeing of the patients. In the best case, patients will be enabled to fully participate again in their normal life in all aspects through the rehabilitation treatment. Since the complex multidisciplinary rehabilitation treatment is very strenuous for the patients as well as very cost intensive for the insurance, it is also essential to prove its effectiveness and quality to avoid unnecessary strain on the patients as well as unnecessary costs. After completion of the study, it is further planned to integrate the assessment instruments into clinical routine, if they prove to be relevant, and to provide these standardized documents to other interested rehabilitation facilities for burn injuries in Germany.

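### The uncontrolled paired tests can show that patients improved, not that the program caused it, so the primary conclusion should be stated as change, and time since injury should join the matching variables

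*Protocol article*

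**What the plan says.** The primary question in the protocol article is causal: "Do the patients benefit from the rehabilitation program regarding their physical and psychological health conditions". The alternative hypothesis under Hypotheses is not. It says only that "Physical and psychological outcome measures are enhanced after burn rehabilitation compared to measures before rehabilitation", with a parallel statement for 3 and 12 months.

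The tests under Statistical methods match the hypothesis rather than the question. "Pre-post comparison (T1–T2) of the outcome measures will be tested by paired one-sided" t tests. The comparisons of T1 with T3 and of T1 with T4 use the same test but carry a causal label: "Longitudinal treatment effects will be tested by paired one-sided" t tests.

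The conclusions announced are causal again. The Discussion paragraph of the Abstract says "The proof of the effectiveness of the ICF-based rehabilitation program for thermal injuries will give evidence". The main Discussion says "The long follow-up period was chosen to prove the long-term effect of the rehabilitation program on the wellbeing of the patients".

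Under Interventions, both centers give their standard rehabilitation program and nothing else. The Discussion acknowledges that the lack of randomization is a limitation and offers the non-inferiority comparison of the two centers to balance it. For that comparison, Statistical methods names five matching variables: age, gender, TBSA, ABSI and inhalation trauma.

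**The concern.** A paired test with no comparator responds to any systematic change between two visits. In this population some change may occur without the program. Under Participants, patients enter once acute treatment is complete, small residual defects are accepted if they are expected to heal soon, and one aim of treatment is to help scars mature. No limit on time since injury is given. Outcomes are then followed to 12 months after discharge.

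The headline conclusion is at stake. The plan intends to declare the program effective and to offer it to other institutions on the strength of tests that would also come out positive if patients had simply recovered. A second, smaller issue concerns the center comparison. Stage of recovery at admission could influence the amount of change, yet it is not among the matching variables.

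**Working it through.** **1. Reproduce the plan's sample size.** The inputs, all from Sample size, are effect size 0.25, pre-post correlation 0.60, one-sided alpha 0.05 and power 0.80.

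- Standardized mean of the paired difference: dz = 0.25 / sqrt(2 × (1 − 0.60)) = 0.25 / sqrt(0.80) = 0.2795.
- Normal approximation: n = ((1.645 + 0.842) / 0.2795)² ≈ 79.1, so 80.
- Exact noncentral t: n = 81, with power 0.802.

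This matches the stated 81 per center. The test is therefore sized to detect a mean change of 0.25 SD, and nothing in the calculation says where that change comes from.

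**2. Set the program effect to zero and let natural improvement supply the change.** The same power function is used, with the mean change equal to an assumed drift. The protocol gives no figure for natural recovery, so the drift values are assumptions shown over a range.

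| Assumed drift (SD) | Significant change, n = 81 | Significant change, n = 162 (centers pooled) |
|---|---|---|
| 0 | 5% | 5% |
| 0.05 | 13% | 18% |
| 0.10 | 26% | 41% |
| 0.20 | 64% | 88% |
| 0.25 | 80% | 97% |

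These figures are per outcome. They are the ordinary power curve of the test. They show how readily it responds to a change that the program did not cause, and they do not estimate how large that change is.

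**3. Consider the interval.** T1 to T2 is short: "The duration of the rehabilitation is planned for 3 weeks in both facilities and can be extended individually". Sample size gives the short intervals between measurements as the reason for expecting only a small-to-medium effect. T4 comes 12 months after discharge, so that reasoning does not carry over to T1 against T4, and there is much more time for recovery unrelated to the program.

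**4. Ask whether center B fills the gap.** Write the mean change at each center as recovery plus program effect:

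- change at A = R + P_A
- change at B = R + P_B
- difference = P_A − P_B

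If R is common to both centers, it cancels. A difference near zero fits two effective programs and equally fits two programs that add nothing. Non-inferiority of A to B therefore says nothing about whether P_A exceeds zero.

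**5. Consider time since injury in the center comparison.** If patients at A and B are admitted at different stages, R is not common and no longer cancels. None of the five matching variables measures stage of recovery. They describe the patient and the severity of the original injury.

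**The case against.** The strongest reply is that the tests do what the hypotheses say. The null hypothesis is that measures do not improve from before to after. If scores rise for any reason, rejecting it is correct. This stands: a reader might take the percentages above as inflated type I error, and they are not. The gap lies between the stated hypothesis and the conclusion drawn from it.

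The design is also openly described as non-randomized, quasi-experimental and observational, for ethical reasons. That is fair, and an untreated group is not being asked for. But the limitation acknowledged is the lack of randomization. Natural recovery is not mentioned, and the remedy offered does not address it (step 4).

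Several stronger readings are tempting, and the document does not support them:

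- *Time since injury is not recorded.* The baseline list is open-ended ("Medical characteristics include diagnosis and therapies, total body surface area (TBSA), partial thickness and full thickness burns", followed by further items), and the article condenses a full protocol and case report form that are not shown. Only the matching variables are a definite list.
- *Length of stay is missing.* It follows from the admission and discharge visits, and the term appears among the abbreviations.
- *Scores will improve by discharge through healing alone.* Entry requires largely stable skin and scars, and the planned stay is 3 weeks. Recovery may contribute by T2. The case is stronger at T3 and T4.
- *Regression to the mean will produce improvement.* Table 2 sets no entry threshold on any outcome score, so the document supplies no mechanism for it.
- *The centers differ in time since injury.* One is on a trauma-center campus and the other in a health resort, but assignment is said to depend on residence and capacity. A difference is possible and is not shown.

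**Conclusion.** The concern holds as a mismatch between test and claim. The primary analysis can establish change during and after the program. It cannot establish that the program caused the change, and the center comparison does not supply the missing evidence. This conclusion rests on the stated design and needs no assumption about how large natural recovery is.

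The size does rest on assumptions. With a correlation of 0.60, 81 patients and no program effect, a drift of 0.10 SD would give a significant change in about one trial in four, and a drift of 0.25 SD in about four in five. The document neither supports nor rules out any particular drift.

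The omission of time since injury from the matching variables is a lesser point, confined to the secondary center comparison. A reader might infer that adjusting for it would rescue the primary claim. It would not, because every enrolled patient is treated and a recovery trend modelled within this sample already contains any program effect.

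**What to change.** 1. Restate the primary conclusion as change during and after the program, and reword three places to match: the Abstract's Discussion sentence ("The proof of the effectiveness of the ICF-based rehabilitation program for thermal injuries will give evidence"), the label in Statistical methods ("Longitudinal treatment effects will be tested by paired one-sided") and the Discussion sentence on follow-up ("The long follow-up period was chosen to prove the long-term effect of the rehabilitation program on the wellbeing of the patients"). In the Discussion, say that natural recovery may contribute and that the center comparison cannot separate it from a program effect.
2. Add time from injury to admission to the matching and propensity-score variables, taking the injury date from the treatment file. Report pre-post change by time since injury as description only.

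Neither change alters a primary test, the sample size or the visit schedule. The cost is a more modest claim, one date per patient that should already be on file, and a sixth variable to match on. The second change reduces possible confounding between centers and should not be presented as identifying a program effect.

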**Trial registration:**

German Clinical Trials Register, DRKS00017702. Registered on 2 September 2019.

## Background

Progress in the medical and surgical management of major burn injuries has significantly increased the likelihood of survival, even in those seriously injured. Since survival from large burns has become more common, mortality is no longer the only relevant outcome measure [1]—functional outcome and quality of life have become more important [2, 3]. Burn injuries result in impaired physical capacity and physical and social integrity and may have a life-long impact on both psychological and physical functioning [4]. The aim of a burn rehabilitation program is to resolve physical and psychological recovery and return into social life and the workplace. During the rehabilitation process, the injured persons and those in their social environment should accept and learn an unbiased handling of the consequences of the injury. These goals can be achieved by helping the person to regain activity and providing behavioral therapy, compensatory strategies (functional adaptation), and assistance in coping with the trauma [5, 6].

There is strong agreement that rehabilitation of patients after burn injuries requires a multidisciplinary team. An increasing number of publications are addressing the relevance of rehabilitation after burn injuries, but structured clinical studies are still rare. Existing studies mostly assess only one special aspect of the treatment program [7–10] or one affected domain such as scarring, quality of life, or mental health [11, 12]. References to the International Classification of Functioning, Disability and Health (ICF) system, a framework which incorporates physical, emotional, environmental, and social aspects of functioning, are rare. In addition to the small overall number of studies, comparison of results and populations is difficult since there are no clear standards for documentation [5, 11].

National and international burn associations provide health care professionals with guidelines for burn rehabilitation [13]. Besides differences in elaborateness, they all confirm the importance of this phase in the treatment of burn injuries. The most clearly defined indications for burn rehabilitation are described in the guidelines of the German Society for Burn Medicine, as listed in Table 1 [6, 14].

**Table 1 Tab1:** Indications for burn rehabilitation

Main indications	Burns degree II ≥ 20% TBSA
	Burns degree III ≥ 10% TBSA
	Burns of face, hands, feet, or genital area
	Scarring with significant limitations of the large joints
Further indications	Remaining functional neurological deficit
	Functional deficits after high-voltage accident
	Limb loss
	Lasting loss of condition and strength
	Problematic psychosocial situation
	Psychiatric disorders after trauma (adjustment disorders, post-traumatic stress reactions, phobic reactions)
	Age more than 50 years
	Thermal accidents in childhood

*TBSA* Total body surface area

Rehabilitation is a comprehensive process involving a multidisciplinary team working in collaboration to optimize patients’ recovery. Main elements of the treatment after burn injuries are rehabilitative nursing for skin and wound care, physical, occupational, and sports therapy, and psychotherapy [15]. Additional support by social workers is needed to advise the patient on the benefits of social security funds and to facilitate the return to work by making contact with the employer and human resources. During the rehabilitation process, consultations involving multiple other medical disciplines such as pain medicine are often needed. Regular meetings of a multidisciplinary team focusing on the quality of patients’ lives are recommended [6].

In rehabilitation center A (BG Trauma Center Ludwigshafen) a new ICF-based specialized burn rehabilitation program was elaborated in 2012 and established in 2014. As a control, the elements of the program and the patients’ outcomes will be compared to those of the well-established burn rehabilitation program of rehabilitation center B. Center B’s program concept was established in 1999 and also includes ICF-based elements. The purpose of the study is to establish standards and evaluate the effectiveness of the programs to meet the requirements of evidence, quality assurance, and cost-effectiveness in the treatment of such complex and costly injury patterns.

